### 4. Post-treatment phase – evaluations after Day 28 (safety follow up):

- a. Medication history at Weeks 12, 24, 36, 48.
- b. Targeted physical examination at Weeks 12, 24, and 36.
- c. Complete physical examination at Week 48.
- d. Hematology evaluations at Weeks 12, 24, 36 and 48.
- e. Blood chemistries and liver function tests at Weeks 12, 24, 36 and 48.
- f. Autoantibodies (ANA, anti-ds-DNA) at Week 48.
- g. Urinalysis at Weeks 12, 24, 36 and 48.
- h. HIV-1 RNA at Weeks 12, 24, 36 and 48.
- i. CD4/CD8 count at Weeks 12, 24, 36 and 48.

- j. Plasma and PBMCs for storage at Weeks 12, 24, 36 and 48.

## 6.1 Schedule of Events

| Evaluations                          | Screening |           | Treatment phase |       |        |        | Safety follow-up |         |
|--------------------------------------|-----------|-----------|-----------------|-------|--------|--------|------------------|---------|
|                                      | Screening | Pre-entry | Day 0           | Day 7 | Day 14 | Day 28 | Weeks 12,24,36   | Week 48 |
| Signed Informed Consent              | X         |           |                 |       |        |        |                  |         |
| Documentation of HIV                 | X         |           |                 |       |        |        |                  |         |
| Medical History                      | X         |           |                 |       |        |        |                  |         |
| Medication History                   | X         |           | X               |       |        | X      | X                | X       |
| Nadir CD4                            | X         |           |                 |       |        |        |                  |         |
| Complete Physical Exam               | X         |           |                 |       |        | X      |                  | X       |
| Targeted Physical Exam               |           |           | X               | X     | X      | X      | X                |         |
| LC002 Administration                 |           |           | X               |       |        |        |                  |         |
| Vaccine Site Local Evaluation        |           |           | X               | X     | X      | X      |                  |         |
| Hematology                           | X         | X         | X               | X     | X      | X      | X                | X       |
| Blood Chemistries                    | X         | X         | X               | X     | X      | X      | X                | X       |
| Liver Function Tests                 | X         | X         | X               | X     | X      | X      | X                | X       |
| Autoantibody Test                    | X         |           |                 |       |        | X      |                  | X       |
| Urinalysis                           | X         | X         | X               | X     | X      | X      | X                | X       |
| Urine Pregnancy Test                 | X         |           | X               |       |        |        |                  |         |
| Hepatitis B and C Screen             | X         |           |                 |       |        |        |                  |         |
| HIV-1 RNA                            | X         | X         | X               | X     |        | X      | X                | X       |
| CD4/CD8 Count and CD45 RA/RO         | X         | X         | X               | X     | X      | X      | X                | X       |
| Virus Specific Immune Response Assay |           |           | X               |       | X      | X      |                  |         |
| Stored plasma and PBMC               |           | X         | X               | X     | X      | X      | X                | X       |

## 6.2 Definitions for Schedule of Events

### 6.2.1 Screening Evaluations

Screening evaluations must occur prior to the subject taking any treatments.

#### Screening

Screening evaluations to determine eligibility must be completed within **3 months** prior to study entry.

#### Pre-entry

Pre-entry evaluations must be completed at least 24 hours after the screening evaluations and within 14 days prior to study entry.

### 6.2.2 On-Study Evaluations

#### Entry

Evaluations should occur after enrollment prior to vaccine administration and at least 24 hours after the pre-entry evaluations.

All subjects will visit the clinic on the weeks  $\pm$  3 days indicated in the Schedule of Events. Vaccine administration has to occur on the weeks indicated in the Schedule of Events  $\pm$  0 days.

### 6.2.3 Evaluations for **eligible** subjects who do not start study treatment

No further evaluations are required.

Subjects passing the screening and/or pre-entry evaluations who, for whatever reason, do not enter the study (Day 0) will not be considered as premature discontinuations.

### 6.2.5 Final Study Evaluations

Week 4 will be the final visit in the study treatment phase. Safety follow up continues to 48 weeks after immunization.

#### 6.2.6 Pregnancy

All female subjects of child-bearing potential must have a negative urine pregnancy test on the day of vaccination. The subject should NOT receive immunizations until the result of the pregnancy test is known to be negative.

### 6.3 Special Instructions and Definitions of Evaluations

#### 6.3.1 Documentation of HIV

HIV-1 infection, as documented by any licensed ELISA test kit and confirmed by Western blot, HIV-1 culture, HIV-1 antigen, plasma HIV-1 RNA, or a second antibody test by a method other than ELISA is acceptable as an alternative confirmatory test at any time prior to study entry.

#### 6.3.2 Medical History

A medical history must be present in source documents and case report forms (CRFs). The medical history should include any previous HIV-related diagnoses and non-HIV-related diagnoses of major organ systems.

Any allergies to any medications and their formulations must be documented.

#### 6.3.3. Medication History

Please note that the medications are to be recorded on the CRFs only when noted.

A medication history must be present in source documents for:

- Complete HIV treatment history, including start and stop dates of any antiretroviral medication (estimated if the exact dates cannot be obtained), immune-based therapy, or HIV-related vaccines, including blinded study medications. All changes in HAART therapy must be documented in the CRF.
- ALL concomitant medications such as prophylactic antimicrobial medications, antifungal, antipyretics, analgesics, allergy medications, oral contraceptives, topical or inhalant corticosteroids will be recorded on the CRF (including doses and start and stop dates) during the course of the study.

- All prescription medications (in addition to those noted above) including those taken within 30 days prior to study entry, including actual or estimated start and stop dates must be recorded in the CRF.
- Nonprescription medications and alternative therapies such as dietary supplements, acupuncture, herbal therapies, and visualization techniques taken within 30 days prior to study entry must be recorded on the CRF. Include actual or estimated start and stop dates.
- History of drug allergy must be recorded on the CRF.

#### 6.3.4 Nadir (lowest) CD4 cell count

The subject's prior nadir CD4 cell count (absolute value and date) should be documented when possible with a copy of the nadir CD4 cell count report and recorded on CRF. If this documentation is not available, then subject recollection will suffice. For subjects who do not know the exact nadir value and for whom there is no source documentation, then recall of the categorical nadir (e.g., <50, 51-100, 101-200, 201-500, >500 cells/mm^3) will suffice.

#### 6.3.5 Complete physical exam

Complete physical examination includes signs and symptoms, diagnoses, Karnofsky score, height, weight, skin and lymph node status, and vital signs (including seated blood pressure, pulse, respirations and oral temperature).

#### 6.3.6 Targeted physical exam

A targeted physical examination including the vital signs (seated blood pressure, pulse, respirations, and oral temperature) must be conducted at study entry and all subsequent visits, to be driven by any signs and symptoms and diagnoses previously identified and any new signs and symptoms or diagnoses that the subject has experienced since the last visit.

#### Signs and Symptoms

At study entry, all signs/symptoms must be recorded. On study, any signs or symptoms that led to a change in treatment, regardless of grade, must be recorded in the CRFs. Record all grades of local reactions and any other signs or symptoms Grade 2 or higher in the CRFs.

All signs, symptoms, HIV-related and AIDS-defining events, deaths, and

toxicities must be documented, and must be recorded in the CRFs within 48 hours throughout the course of the study.

Refer to the Division of AIDS Table for Grading Adult Adverse Experiences for toxicity grading.

#### Diagnoses

All confirmed and probable diagnoses and any clinical events made since the last visit must be recorded in the source document and the CRF.

#### 6.3.7 LC002 administration/evaluation

The first vaccine site evaluation (see section 7.1.1) will be performed immediately after removal of the skin patch (3h post application). Further vaccine site evaluation must occur on the days indicated in the Schedule of Events.

### LABORATORY EVALUATIONS

Any laboratory toxicities that led to a change in treatment, regardless of grade, must be recorded in the CRFs. At baseline, record all laboratory values. For post-baseline assessments, all laboratory values must be documented in the subject's record, but only laboratory values Grade > 2 must be recorded in the CRFs.

All Grade  $\geq$  2 laboratory results must be recorded on the CRFs within 48 hours throughout the course of the study.

Refer to the Division of AIDS Table for Grading Adult Adverse Experiences (see Appendix IV) for toxicity grading.

#### 6.3.9 Hematology

Hemoglobin, hematocrit, white blood cell count (WBC), absolute neutrophil count (ANC) and platelets.

#### 6.3.10 Blood Chemistries

Albumin, BUN, electrolytes, creatinine.

#### 6.3.11 Liver Function Tests

ALT, AST, alkaline phosphatase, total bilirubin.

#### 6.3.12 Autoantibody Test

Anti-nuclear antibody (ANA), anti-double-stranded DNA antibody (anti-ds-DNA)

#### 6.3.13 Urinalysis

Urinalysis (dipstick).

#### 6.3.14 Urine pregnancy testing

For women with reproductive potential: a urine  $\beta$ -HCG test with a sensitivity of 25-50 mIU/mL. The pregnancy test must be negative before vaccine administration.

#### 6.3.15 Hepatitis B and C screen

Hepatitis B surface antigen and anti-hepatitis C antibodies, to be performed locally.

#### 6.3.16 Plasma HIV-1 RNA

The screening HIV-1 RNA must have been performed locally within three months of entry. Eligibility will be determined based on the screening value. The pre-entry HIV-1 RNA must be performed within 14 days prior to study entry. The baseline value will be the geometric mean of the pre-entry and entry determination. All tests will be performed locally.

Additional laboratory evaluations (not considered in the Division of AIDS Table for Grading Adult Adverse Experiences):

Red blood cell count (RBC), granulocytes, lymphocytes, monocytes, eosinophils, basophils, prothrombin time, creatinine, amylase, LDH, glucose, total protein, cholesterol and triglycerides, C-reactive protein, direct bilirubin, albumin.

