## 4.0 SELECTION AND ENROLLMENT OF SUBJECTS

### 4.1 Inclusion Criteria

- 4.1.1 Ability and willingness of subject or legal guardian/representative to give written informed consent.
- 4.1.2 HIV-1 infection, as documented by any licensed ELISA test kit and confirmed by Western blot, HIV-1 culture, HIV-1 antigen, plasma HIV-1 RNA, or a second antibody test by a method other than ELISA is acceptable as an alternative confirmatory test at any time prior to study entry.
- 4.1.3 On a stable antiretroviral regimen (containing drugs of at least two different classes) without changes or interruptions for at least 24 weeks prior to study entry.
- 4.1.4 Plasma HIV-1 RNA level of less than 50 copies/mL, while on a stable antiretroviral regimen, obtained at least twice within the 12 weeks prior to study entry.
- 4.1.5 Peak plasma HIV-1 RNA level before initiation of HAART > 1000 copies/mL.
- 4.1.6 CD4 cell count > 300 cells/mm^3 within the 12 weeks prior to study entry.
- 4.1.7 Nadir (lowest) CD4+ cell count > 250 cells/mm^3 at any time prior to study entry.
- 4.1.8 The following laboratory values, obtained within 30 days prior to study entry:
  - Absolute neutrophil count (ANC)  $\geq 1000/\text{mm}^3$
  - Hemoglobin  $\geq 9.0$  g/dL
  - Platelet count  $\geq 50,000/\text{mm}^3$
  - Serum creatinine  $\leq$  upper limit of the laboratory normal range (ULN)
  - AST (SGOT), ALT (SGPT), and alkaline phosphatase  $\leq 2.5 \times \text{ULN}$
  - Total bilirubin  $\leq 2.5 \times \text{ULN}$

- Anti-nuclear antibody (ANA) titer of 1:40 or lower and negative for serum anti-double-stranded DNA antibody (anti-ds-DNA) test result at screening.

- 4.1.9 All women of reproductive potential (who have not reached menopause or undergone hysterectomy, oophorectomy, or tubal ligation) must have a negative urine  $\beta$ -HCG pregnancy test performed within 14 days prior to study entry.

Female study volunteers who are not of reproductive potential (who have reached menopause or undergone hysterectomy, oophorectomy, or tubal ligation) or whose male partner has undergone successful vasectomy with documented azoospermia or has documented azoospermia for any other reason, are eligible without requiring the use of contraception. Acceptable documentation of menopause, sterilization, and azoospermia is written or oral documentation communicated by clinician or clinician's staff of one of the following:

- Physician report/letter

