## 4.2 Exclusion Criteria

4.2.1 Viral load measurement  $>$  50 copies/mL within the last 12 weeks prior to study entry.

4.2.2 History of or evidence of active skin disease (atopic dermatitis, psoriasis, etc.), chronic autoimmune disease or any other significant active skin disease.

4.2.3 Treatment with topical corticosteroids in close proximity to the proposed vaccination sites within 2 weeks prior to study entry.

4.2.4 Excessive exposure to the sun (e.g., sunbathing, tanning bed) within 2 weeks prior to study entry.

4.2.5 Use of any local skin treatments to the targeted vaccination sites within 7 days prior to study entry.

4.2.6 History of diabetes and bleeding disorders.

4.2.7 Previous CDC category C event as defined in Appendix I.

4.2.8 Pregnancy or breast-feeding.

4.2.9 Use of immunomodulating therapy, including cyclosporin, IgG-containing products, interleukins, interferons, systemic glucocorticosteroids, or exposure to an experimental HIV vaccine within 6 months prior to study entry.

4.2.10 Receipt of any vaccine within 30 days prior to study entry.

4.2.11 Allergy/sensitivity to study vaccine products, including adhesives, will be excluded.

4.2.12 Active drug or alcohol use or dependence that, in the opinion of the investigator, would interfere with adherence to study requirements.

4.2.13 Serious illness until subject either completes therapy or is clinically stable on therapy, in the opinion of the site investigator, for at least 14 days prior to study entry.

4.2.14 Hepatitis B surface antigen and/or anti-hepatitis C positive.

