#### 4.3 Study Enrollment Procedures

4.3.1 Prior to implementation of this protocol, the protocol and consent form must be approved by the local institutional ethics committee.

Once a candidate for study entry has been identified, details will be carefully discussed with the subject. The subject (or parent or legal guardian if the subject is under guardianship) will be asked to read and sign the consent form.

Only subjects who meet the eligibility criteria at both the screening and pre-entry visits will be enrolled. Cohorts will enroll serially. After all 3 subjects of a given cohort (#1 or #2) have received their study vaccine administrations, and have remained on study through at least the 14th day, if no subject in any cohort has experienced a Primary Safety endpoint (defined in section 9.2.1), then the study will dose escalate by opening enrollment of subjects into the next cohort.

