### IMMUNOLOGIC STUDIES

#### 6.3.17 CD4/CD8

Obtain absolute CD4/CD8 count and percentages within 14 days prior to study entry from a laboratory. Eligibility for study participation will be determined by the screening measurement, which has to be obtained within three months of entry. A mean of the pre-entry and entry measurements will be used as the baseline value.

Evaluations for CD4+ and CD8+ counts and subset percentage evaluations should be performed at the same laboratory, if possible, for baseline calculation and throughout the course of the study.

Because of the diurnal variation in CD4+ and CD8+ cell counts, determinations for individual subjects should be obtained consistently in either the morning or the afternoon throughout the study, if possible.

NOTE: Each time a CD4/CD8 measurement is obtained, the local laboratory must perform a WBC and differential from a sample obtained at the same time.

Additional cell surface markers (CD45RA, CD45RO) will be evaluated to determine naïve/memory phenotype of CD4 and CD8 T cells.

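### HIV-1 RNA eligibility rests on one screening value in 6.3.16 but on stricter rules in 4.1.4, 4.2.1 and 4.3.1; the CD4, nadir CD4 and Karnofsky rules also need reconciling

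*Protocol*

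**What the plan says.** **HIV-1 RNA.** Section 6.3.16 says "Eligibility will be determined based on the screening value" and allows that value to date from any time within three months of entry. It requires a pre-entry value within 14 days of entry, but uses it only for the baseline (geometric mean of pre-entry and entry). Elsewhere:
- 4.1.4 requires a level under 50 copies/mL, "obtained at least twice within the 12 weeks prior to study entry".
- 4.2.1 excludes a viral load above "50 copies/mL within the last 12 weeks prior to study entry".
- 4.3.1 states: "Only subjects who meet the eligibility criteria at both the screening and pre-entry visits will be enrolled".

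**CD4.** Section 6.3.17 says "Eligibility for study participation will be determined by the screening measurement, which has to be obtained within three months of entry". Section 4.1.6 asks for a count above 300 within 12 weeks. Section 3.0 places the same threshold at the time of entry.

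**Nadir CD4.** Section 4.1.7 requires "Nadir (lowest) CD4+ cell count > 250 cells/mm"³. Under 6.3.4, where there is neither a report nor an exact figure, it is enough to have "recall of the categorical nadir (e.g., <50, 51-100, 101-200, 201-500, >500 cells/mm"³).

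**Karnofsky.** Section 4.1.11 requires a score of at least 90 within 30 days of entry. The score belongs to the complete physical examination (6.3.5). Before entry, the schedule in 6.1 has that examination only at screening, which 6.2.1 allows up to three months ahead.

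**The concern.** Section 6.3 holds the instructions that a site is likely to have open when it orders and reads a test. If those instructions give a different eligibility rule from section 4, two sites, or one site on two occasions, can decide differently on the same subject. The protocol states no order of precedence between the sections. With nine subjects in three cohorts of three, one wrongly admitted subject is a large part of the data. The nadir rule differs in kind: following 6.3.4 as written can admit someone who does not meet 4.1.7, without anyone departing from the text.

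**Working it through.** The protocol gives no figure on this point to reproduce. The check compares the rules and adds simple arithmetic.

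**1. RNA rules applied to one case.** Take a subject below 50 copies/mL at screening and at 300 copies/mL at pre-entry.
- 6.3.16: eligible, because the screening value decides.
- 4.1.4: not established by these results, since only one of them is below 50 and two are needed.
- 4.2.1: excluded, because the pre-entry value lies above 50 and within 12 weeks.
- 4.3.1: not enrolled, because the criteria are not met at pre-entry.

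The sentence in 6.3.16 therefore gives the opposite answer to 4.2.1 and 4.3.1.

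**2. Windows.** 12 weeks = 12 × 7 = 84 days. Three calendar months = 89 to 92 days. The differences are 89 − 84 = 5 and 92 − 84 = 8 days. A screening RNA or CD4 value can meet 6.3.16 or 6.3.17 and lie 5 to 8 days outside the window in 4.1.4 or 4.1.6.

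**3. CD4 rules.** Section 4.1.6 asks for one count and no repeat, so in number of values it agrees with 6.3.17. The conflicts with 6.3.17 are three: section 3.0 (at entry), 4.3.1 (criteria met at two visits) and the 12-week window of 4.1.6.

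**4. Nadir categories against the cut-off of 250.**
- Under 50, 51-100 and 101-200: all fail.
- Over 500: all pass.
- 201-500: undetermined. Integer values in the category: 500 − 201 + 1 = 300. Values at or below 250: 250 − 201 + 1 = 50. Share failing if values are spread uniformly: 50/300 = 16.7%.

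The uniform spread is an assumption; the protocol gives no distribution of nadirs. That the category cannot settle 4.1.7 needs no assumption.

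**5. Karnofsky.** A subject screened 60 days before entry can complete every scheduled visit without a score inside the 30-day window. A subject screened within 30 days meets both rules. The schedule permits the gap but does not force it.

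**6. Size.** One subject is 1/3 = 33% of a cohort and 1/9 = 11% of the trial. The protocol gives no rate at which subjects pass RNA at screening and fail at pre-entry. If that chance is an assumed p, independent between subjects, and if sites let 6.3.16 override 4.2.1 and 4.3.1, the chance of at least one such subject among nine is 1 − (1 − p)⁹:

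| Assumed p | At least one of 9 |
|---|---|
| 0.02 | 17% |
| 0.05 | 37% |
| 0.10 | 61% |
| 0.15 | 77% |

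If 4.2.1 and 4.3.1 are followed, this route is closed.

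**The case against.** The strongest reply is that the protocol as a whole already protects entry. A reader might infer from 6.3.16 that viraemic subjects will be enrolled. The documents do not support that, because 4.2.1 and 4.3.1 each bar such a subject. Enrolment would need a site to put a sentence from the evaluation instructions above an exclusion criterion and the enrolment rule. This stands and limits the RNA point to a contradiction that could mislead a site.

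Three other inferences also fail.
- *Pre-entry viraemia would be read as a vaccine effect.* Section 6.3.16 builds the baseline from pre-entry and entry values, so the raised value would show in the baseline, and objective 1.2.4 concerns changes in viral load. The primary safety endpoint (9.2.1) is adverse events of grade 3 or higher judged related to treatment, and the escalation rule (9.1.3) rests on that endpoint and on time on study. Neither uses an RNA threshold.
- *Section 4.1 requires repeated CD4 counts.* It does not; 4.1.6 asks for one.
- *The ANA and anti-ds-DNA tests are scheduled against their own criterion.* That bullet in 4.1.8 sits under a 30-day heading but itself refers to the screening result, so testing at screening is not a contradiction.

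On the nadir, it is fair to say that the categories are examples, that only one of the five straddles the cut-off, that recall by category is a last resort, and that 4.1.7 still applies. But 6.3.4 says such recall is enough, and the one straddling category is where the decision falls. That objection narrows the number of subjects concerned; it does not repair the rule.

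**Conclusion.** The point holds in limited form. Section 6.3.16 contradicts 4.1.4, 4.2.1 and 4.3.1 on RNA, and the three-month and 12-week windows differ by 5 to 8 days. Section 6.3.17 conflicts with 3.0, with 4.3.1 and with the window in 4.1.6. The example category 201-500 in 6.3.4 cannot establish a nadir above 250. The Karnofsky schedule does not guarantee its 30-day criterion.

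The nadir rule is the one most able to admit an ineligible subject while the text is being followed. How often is unknown: 16.7% of those admitted on that category under an assumed uniform spread, and only among subjects with no report and no exact recall. The RNA contradiction lets in a viraemic subject only if 6.3.16 is allowed to override section 4. No sample-size or error-rate figure is affected. The correction is worth making because the entry rules of a nine-subject trial should give a single answer.

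**What to change.** - **6.3.16:** remove the sentence that rests eligibility on the screening value, and refer to 4.1.4, 4.2.1 and 4.3.1.
- **6.3.17:** reconcile with 3.0, 4.1.6 and 4.3.1. The sponsor should state which CD4 value or values govern.
- **Windows:** for RNA and CD4, align three months with 12 weeks in the screening paragraph of 6.0, in 6.2.1, 6.3.16 and 6.3.17.
- **6.3.4:** split the recall category at the protocol's own cut-off, into 201-250 and 251-500, so that a recalled category can establish 4.1.7.
- **Karnofsky:** reconcile the 30-day window in 4.1.11 with the visit schedule in 6.1.

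The cost is small. Pre-entry RNA and CD4 are already in the schedule in 6.1, so those changes are wording only. Expect a few more screen failures, and an occasional repeat Karnofsky score when screening is more than 30 days old.

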#### DURATION:

Subjects will be on study for a total of 4 weeks followed by an additional 48 weeks for safety evaluations.

SAMPLE SIZE: 9 subjects (3 subjects/cohort)

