#### 9.1.3 Dose Escalation Rule

Dose escalation will occur if

- 1) at least 2 subjects were on study until at least 14 days after receiving their study vaccination and
- 2) no subject in the current or lower dose cohort experienced a Primary Safety Endpoint.

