### 9.2 Endpoints

#### 9.2.1 Primary endpoint: Safety

Occurrence of at least one grade 3 or higher adverse event including signs/symptoms, lab toxicities and clinical events that is "possibly, probably," or "definitely" related to study treatment (as judged by the Principal Investigator, including site clinicians on the team) any time from the first day of study treatment until 28 days after LC002 administration.

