#### MISCELLANEOUS

- When two values are used to define the criteria for each parameter, the lowest values will be first.
- Parameters are generally grouped by body system.
- Some protocols may have additional protocol specific grading criteria.

| PARAMETER          | GRADE 1                  | GRADE 2                  | GRADE 3                  | GRADE 4                      |
|---------------------------|---------------------------------|---------------------------------|---------------------------------|-------------------------------------|
|                           | MILD                     | MODERATE                 | SEVERE                   | POTENTIALLY LIFE-THREATENING |
| HEMATOLOGY  |                                 |                                 |                                 |                                     |
| Hemoglobin                | 8.0 g/dL - 9.4 g/dL             | 7.0 g/dL - 7.9 g/dL             | 6.5 g/dL - 6.9 g/dL             | <6.5 g/dL                           |
| Absolute Neutrophil Count | 1000 - 1500/mm      | 750 - 999/mm        | 500 - 749/mm        | <500/mm                 |
| Platelets                 | 75,000 - 99,000/mm  | 50,000 - 74,999/mm  | 20,000 - 49,999/mm  | <20,000/mm              |
| Prothrombin Time (PT)     | >1.0 - 1.25 x ULN               | >1.25 - 1.5 x ULN               | >1.5 - 3.0 x ULN                | >3 x ULN                            |
| PTT                       | >1.0 - 1.66 x ULN               | >1.66 - 2.33 x ULN              | >2.33 - 3.0 x ULN               | >3.0 x ULN                          |
| Methemoglobin             | 5.0 - 10.0%                     | 10.1 - 15.0%                    | 15.1 - 20.0%                    | >20%                                |
| CHEMISTRIES |                                 |                                 |                                 |                                     |
| SODIUM             |                                 |                                 |                                 |                                     |
| Hyponatremia              | 130 - 135 meq/L                 | 123 - 129 meq/L                 | 116 - 122 meq/L                 | <116 meq/L                          |

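### Section 6.3.16 places 17 additional tests outside the toxicity table, but Appendix IV grades five of them, so a Grade 3 or higher value could miss the CRF and the primary safety endpoint

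*Protocol*

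**What the plan says.** The last paragraph of Protocol Section 6.3.16 (Plasma HIV-1 RNA) adds a set of tests under the label "Additional laboratory evaluations (not considered in the Division of AIDS Table for Grading Adult Adverse Experiences". After six blood-count items, the list continues with "prothrombin time, creatinine, amylase, LDH, glucose, total protein, cholesterol and triglycerides, C-reactive protein, direct bilirubin, albumin".

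Appendix IV reproduces the Division of AIDS table. Its Hematology block has a row for "Prothrombin Time (PT)". Its Chemistries block has rows for creatinine, low glucose, high glucose and triglycerides, and its Pancreatic Enzymes block has one for amylase.

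Three other provisions turn on the grade:

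- Section 9.2.1 defines the primary endpoint as "Occurrence of at least one grade 3 or higher adverse event including signs/symptoms, lab toxicities and clinical events", if judged possibly, probably or definitely related, from the first day of treatment to 28 days after administration.
- Section 9.1.3 allows escalation only if "no subject in the current or lower dose cohort experienced a Primary Safety Endpoint".
- The Laboratory Evaluations text in Section 6.3 keeps all post-baseline values in the subject's record, "but only laboratory values Grade > 2 must be recorded in the CRFs". The same text also requires entry of any laboratory toxicity that led to a treatment change, whatever its grade, and refers to Appendix IV for grading.

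**The concern.** The label in 6.3.16 is untrue for some of the tests beneath it, and it concerns the table that determines the primary endpoint. If staff take the label at face value, they have no cause to look these tests up in Appendix IV. A value that the table would call Grade 3 may then carry no grade or a lower one.

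Escalation tolerates no events in cohorts of three (Schema; Section 3.0), so a single value can decide whether the next cohort opens. Recovery after the fact would also be difficult. The value would be in the subject's record, but with no grade attached the protocol would not require it in the CRF. An analysis plan cannot count an event that the database does not hold, so this has to be settled in the protocol.

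**Working it through.** There is no plan figure to reproduce, so the check sets the passages against each other.

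**Step 1: count the list.** Section 6.3.16 names red cells, granulocytes, lymphocytes, monocytes, eosinophils and basophils (6); prothrombin time, creatinine, amylase, LDH, glucose, total protein, cholesterol and triglycerides (8); C-reactive protein, direct bilirubin and albumin (3). 6 + 8 + 3 = 17.

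**Step 2: match each test to a row of its own in Appendix IV.** Five match, on six rows because glucose has two.

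| Test | Grade 3 | Grade 4 | In a panel of 6.3.9 to 6.3.11? |
|---|---|---|---|
| Prothrombin time | >1.5–3.0 × ULN | >3 × ULN | No |
| Creatinine | >3.0–6.0 × ULN | >6.0 × ULN | Yes (6.3.10) |
| Amylase | >2.0–5.0 × ULN | >5.0 × ULN | No |
| Glucose, low | 30–39 mg/dL | <30 mg/dL | No |
| Glucose, high | 251–500 mg/dL | >500 mg/dL | No |
| Triglycerides | 751–1200 mg/dL | >1200 mg/dL | No |

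The high-glucose row is for nonfasting values without prior diabetes. Section 4.2.6 excludes a history of diabetes, so the row fits the enrolled population. The label is therefore wrong for 5 of the 17 tests.

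**Step 3: follow one value through.** Take a triglyceride result between 751 and 1200 mg/dL, after vaccination and within 28 days, in a subject without symptoms.

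- *Graded by its row in Appendix IV:* Grade 3. CRF entry is required. If judged related, it is a primary endpoint under 9.2.1 and blocks escalation under 9.1.3.
- *Treated as absent from the table, with Appendix IV's general severity scale used instead:* that scale rests on limitation of activity and need for intervention. With no limitation and no intervention, the value fits the Grade 1 description. It is below the CRF threshold and is not an endpoint.
- *Treated as not gradable:* no grade, so no grade-based trigger for CRF entry, and it is not an endpoint.

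In the second and third cases, only a resulting change of treatment would bring the value into the CRF. The Laboratory Evaluations text gives its threshold once as above Grade 2 and once as Grade 2 or higher. The difference does not matter here, since Grade 3 meets both.

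**Step 4: separate creatinine from the rest.** Creatinine is an entry criterion (4.1.8) and a scheduled chemistry (6.3.10; Section 6.1) as well as a graded row, so a site would meet it by another route. Prothrombin time, amylase, glucose and triglycerides have no such route. They are in no named panel, and Section 6.1 has no row for the additional tests.

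**Step 5: size.** The protocol gives no rate for related Grade 3 or higher values of these tests, so the effect on the endpoint or on escalation cannot be calculated from it.

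**The case against.** The strongest reply is that 6.3.16 instructs nobody to leave anything ungraded. The phrase is a descriptive aside under the HIV-1 RNA heading, while the operative text points to Appendix IV. The Laboratory Evaluations text sends laboratory values there for grading, Section 7.1.2 does the same for systemic reactions, and 9.2.1 counts laboratory toxicities without excepting any test. This stands, and it limits the point: the omission arises only if a site relies on the aside. But the aside is the only text specific to these tests, so such reliance is plausible.

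A second reply is that Appendix IV has a scale for abnormalities not found in the table, so nothing is truly ungraded. That holds in part. The scale is meant for abnormalities without a row, which these five have, and Step 3 shows that it can give a lower grade when there are no symptoms.

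A reader might infer that the plan excludes these tests from the primary endpoint. It does not; 9.2.1 contains no such exclusion. A reader might also assume a rate q and take 1 − (1 − q)³ as the chance that a cohort's decision changes. That formula gives the chance of at least one such event in three subjects. A changed decision also requires that every such value goes uncounted and that the cohort has no other endpoint, so the formula is an upper bound on an assumed rate. It would also apply a 28-day window although escalation can open at Day 14 (4.3, 9.1.3), and Cohort 3 has no later escalation to affect.

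**Conclusion.** The contradiction is certain, and the five tests are the complete set with rows of their own. It is more than clerical, because CRF entry, the primary endpoint and the escalation rule all depend on the grade. The consequence is conditional. A value is lost only if a site follows the label in 6.3.16, the value is Grade 3 or higher by Appendix IV, it would have been judged related, and no treatment change brings it into the CRF. The exposure lies mainly with prothrombin time, amylase, glucose and triglycerides, and is weaker for creatinine. No probability should be attached to it.

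**What to change.** Reconcile 6.3.16 with Appendix IV by removing prothrombin time, creatinine, amylase, glucose and triglycerides from the list described as outside the table. Add a sentence confirming that, whenever these tests are measured, they are graded by their rows in Appendix IV, entered in the CRF under the Laboratory Evaluations rule, and assessed under 9.2.1 like any other laboratory toxicity. The definition in 9.2.1 and the rule in 9.1.3 need no change.

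The cost is a short wording amendment, best made before the first cohort is dosed. The small downside is that a few more laboratory values may count as safety events.

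Separately, the protocol should make clear when the additional tests are drawn, since neither the text of Section 6.0 nor the schedule in 6.1 says. The wording fix does not depend on that and does not require extra visits or samples.
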